### Data analysis

Multiple imputation of missing data will be performed for intention-to-treat analyses. Before running all analyses, all variable distributions will be screened for normality assumptions and univariate outliers. The use of parametric or non-parametric statistical tests will be adjusted accordingly. Each training group will be compared to its control group to check for any baseline difference in demographics (e.g., age and gender), severity of gambling problems (SOGS), and alcohol use. When significant differences are found and the relevant baseline variables also correlate with the outcomes of interest, they will be added as covariates in subsequent analyses.

Changes in gambling frequency and expenditure from baseline to the 6-month follow up will be examined through two separate 2 (condition: active training vs. placebo) × 4 (time: baseline, post-intervention, 3-month and 6-month follow up) mixed analysis of variance (ANOVA) analyses, one per training module. Each CBM condition is contrasted against its control condition, with the baseline assessment as reference time point for the following time points.

Changes in gambling cognitive biases as a result of each CBM intervention will be explored with a 3 (time: baseline, post-intervention, 3-month follow up) × 2 (condition: active vs. placebo training) × 2 (stimulus category: gambling vs. control) mixed ANOVA for approach bias (i.e., AAT task) and a 3 (time: baseline, post-intervention, 3-month follow up) × 2 (condition: active vs. placebo training) × 2 (trial type: on top vs. after) mixed ANOVA for attentional bias (i.e., VPT task). Any change in depression symptoms and gambling problems would be explored using two 2 (condition: active vs. placebo training) × 4 (time: baseline, post-intervention, 3-month and 6-month follow-up) mixed ANOVA analyses, one per training module.

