No multiplicity adjustment will be applied to correct for the multiple treatment arms since the two active training conditions are distinct treatments, compared to their own control condition. As mentioned earlier, in order to efficiently explore the main effects of both types of training modules, the design of the study involves running two clinical trials under the same protocol. Hence, the two trials can be considered as separate studies, making it unconventional to apply any adjustments to alpha levels. Furthermore, we emphasize that the study is strictly explorative in nature, so any significant findings should be received with some reservation until tested in further confirmatory RCTs, implying a lesser need for multiple-testing correction [67].

If significant effects of the CBM interventions on the cognitive bias and gambling outcomes are detected, a moderated mediation analysis for each CBM module will be carried out to explore the moderating effect of interference control capacity, impulsivity and baseline cognitive bias on the relation between CBM effects and the gambling outcome(s) [68]. Baseline cognitive biases, interference control capacity (Stroop task) and trait impulsivity (BIS-11) would be tested as moderators of the changes in cognitive bias resulting from training, which would further act as mediator of the change in the primary outcome(s).

Besides monitoring participant inclusion and drop-out, the analysis plan does not involve any interim analysis of collected data. The clinical trial will continue until the target sample size is reached unless participant attrition rate, defined as a drop-out at any moment after completing the baseline assessment, exceeds the expected 60% attrition rate of included participants [42]. The results of the study will be reported following the guidelines of the “Consolidated standards of reporting trials” (CONSORT) extension to non-pharmacological interventions [69].

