### Sample size

A conservative a priori power analysis (G*Power 3.1, open-source software [70]) required a sample size of 114 participants to detect a small-to-medium effect size (Cohen’s *f* = 0.15, equivalent to partial eta squared value of 0.02) for the interaction effect between time and experimental condition for each primary outcome, using mixed ANOVA. Power of 0.80, Bonferroni-adjusted type-I error probability of 0.025 (0.05/2 primary outcomes) and moderate correlation between the repeated measures of 0.3 were assumed. Based on a similar online CBM study for alcohol drinking problems [42], an additional 60% dropout rate at follow up was taken into account, leading to a final target sample size of 182 participants.

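### The 60% dropout allowance was added to 114 (114 × 1.6 = 182) instead of being divided out (114 / 0.40 = 285), so 182 randomised leaves about 73 completers, not 114

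*Protocol article*

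**What the plan says.** The Sample size section reports that an a priori power analysis "required a sample size of 114 participants to detect a small-to-medium effect size", given as Cohen's f = 0.15 and described as "equivalent to partial eta squared value of 0.02". The test is the interaction of time and condition in a mixed ANOVA. The other settings are "Power of 0.80, Bonferroni-adjusted type-I error probability of 0.025 (0.05/2 primary outcomes") and "moderate correlation between the repeated measures of 0.3 were assumed".

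The section then states that "an additional 60% dropout rate at follow up was taken into account, leading to a final target sample size of 182 participants". It prints no inflation formula. The Abstract repeats N = 182.

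The Data analysis section uses the same 60% in its rule for ending recruitment early. The trial runs to its target "unless participant attrition rate, defined as a drop-out at any moment after completing the baseline assessment, exceeds the expected 60% attrition rate", and the sentence goes on to refer that rate to included participants. Under Randomisation, allocation follows completion of the baseline session, so this attrition is counted from the point of randomisation.

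The primary outcomes are analysed by "2 (condition: active training vs. placebo) × 4 (time: baseline, post-intervention, 3-month and 6-month follow up) mixed analysis of variance", with one such analysis per training module. Multiple imputation is planned for the intention-to-treat analyses.

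**The concern.** A dropout rate is a proportion of those who start. To end with n evaluable participants when a fraction d is lost, one randomises n / (1 − d). Multiplying by (1 + d) gives a similar answer when d is small, but the two diverge sharply as d grows, and at 60% the gap is very large. The step from 114 to 182 looks like the multiplying form.

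If so, the dropout allowance does not protect the number that the power analysis asked for. The stated power of 0.80 would then not hold under the dropout that the protocol itself expects, and a reader of the Sample size section would credit the trial with more information at follow-up than its own assumptions allow.

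**Working it through.** **Inputs.** From Sample size: 114 required; f = 0.15, or partial eta squared 0.02; power 0.80; alpha 0.025; correlation 0.3; dropout 60%; target 182. From Data analysis: 2 conditions × 4 time points, and 60% counted among included participants after baseline.

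**Step 1: reproduce 114.** For the within-between interaction in a repeated-measures ANOVA with k = 2 groups and m = 4 times, the noncentrality is λ = f² × N × m / (1 − ρ), with df1 = (k − 1)(m − 1) = 3 and df2 = (N − k)(m − 1).

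- Partial eta squared 0.02 gives f² = 0.02 / 0.98 = 0.0204, so f = 0.143. The smallest N with power 0.80 is 113, or 114 with equal groups. At N = 114, λ = 0.0204 × 114 × 4 / 0.7 = 13.29, df2 = 336, and power is 0.807. The stated figure reproduces.
- The rounded f = 0.15 gives N = 102, so 114 evidently rests on the eta-squared value.

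So 114 is the number needed with data in a single two-group comparison.

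**Step 2: reproduce 182.**

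- n × (1 + d) = 114 × 1.60 = 182.4, which rounds to 182. This matches.
- n / (1 − d) = 114 / 0.40 = 285. This does not match.

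The factor 1.6 is inferred, because the formula is not printed, but it gives the stated figure and the standard inflation does not.

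**Step 3: what 182 delivers.**

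- Expected completers at 60% dropout: 182 × 0.40 = 72.8, about 73.
- Shortfall: (114 − 73) / 114 = 36%.
- Dropout at which 182 still leaves 114: 1 − 114 / 182 = 37.4%.
- Number randomised for 114 completers: 285, which is 285 − 182 = 103 more than the target.

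**Step 4: power at 73 (illustrative).** This assumes complete cases only, all 73 in one two-group comparison, alpha 0.025, ρ = 0.3 and df2 = 71 × 3 = 213.

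| Effect size | λ | Power at N = 73 |
|---|---|---|
| partial eta squared 0.02 (f = 0.143) | 0.0204 × 73 × 4 / 0.7 = 8.51 | 0.57 |
| f = 0.15 | 0.0225 × 73 × 4 / 0.7 = 9.39 | 0.62 |

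**Step 5: direction of the remaining uncertainty.** Under the allocation 1:1:0.62:0.62, each module's comparison receives (1 + 0.62) / 3.24 = 50% of the sample: 91 of 182 randomised and about 36 completers at 60% dropout. The same formula then gives power of 0.26 to 0.29. The protocol does not say whether 114 was meant per module or in total. That is a separate question, and the finding does not depend on it.

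**The case against.** **The wording could mean recruiting 60% extra.** That reading would yield 182, but the sentence calls the 60% a dropout rate, and the Data analysis section ties it to included participants. It cannot be read as a recruitment margin.

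**Multiple imputation keeps everyone in the analysis.** Imputation keeps all randomised participants in the dataset, but it does not recreate follow-up outcomes that were never observed. The protocol inflated for dropout, so it already accepted that dropout costs information.

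**The power figure is not exact.** This stands. Attrition is counted from any time after baseline, so someone lost after the post-intervention or 3-month visit counts as a dropout and still contributes data. The timing of dropout is not given, so the true loss of power cannot be determined. A reader might infer that 60% of participants contribute nothing; the documents do not support that. The range 0.57 to 0.62 is a complete-case illustration. The split by module works in the other direction.

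**The trial is an exploratory pilot.** This also stands in part. The protocol asks that significant findings be treated with reserve and sees the study as generating hypotheses. It would go too far to say that a null result will be taken as coming from an adequately sized trial. The Sample size section nevertheless makes a formal power claim, and that claim should match its own assumptions.

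**The early-ending rule.** A reader might infer that the 60% figure is misused a second time, because the threshold for ending recruitment equals the planning value. The text does not support this. The rule applies only when attrition exceeds 60%, which is a coherent feasibility guard, and no schedule of looks is given from which a chance of stopping could be calculated.

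**Conclusion.** The target of 182 is wrong as an allowance for 60% dropout from 114. The matching number is 285. At 182 randomised the plan's own assumption leaves about 73 completers, 36% below requirement, and the requirement is met only if dropout stays at or below about 37%. The arithmetic rests on two things in the text: 114 is the number needed with data, and 60% is a share of those included and followed from baseline. The method by which 182 was reached is inferred from the figures.

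The stated power of 0.80 is therefore not supported at the expected dropout. The illustrative complete-case value is 0.57 to 0.62 with all completers in one comparison, subject to the two opposing influences above.

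On the early-ending rule, only one consequence follows: with attrition between about 37% and 60%, the trial continues to its target without the 114 that it says it needs.

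**What to change.** Correct the Sample size statement so that the inflation is shown: 114 completers at 60% dropout corresponds to 114 / 0.40 = 285 randomised.

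If 182 is kept, say that about 73 participants are expected to complete. In place of 0.80, give the power or the detectable effect at that number, with its assumptions: complete cases or partial follow-up, and whether the figure is per module or overall.

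Keeping 182 needs only a change of wording and no extra participants; the cost is a less favourable stated power. Raising the target to 285 would mean 103 more participants. That is a choice for the sponsor and is not required to correct the statement. Recruitment was still open according to Trial status, so the correction can be made before the outcome data are analysed.

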## Discussion

The goal of this pilot, double-blind RCT is to develop and explore the effectiveness of two online CBM interventions targeting maladaptive implicit motivational processes underlying problematic and pathological gambling behaviour, namely selective attention and automatic approach tendencies towards gambling cues. To the best of our knowledge, this is the first study evaluating the potential effects of CBM interventions on gambling behaviour. The results would expand previous research on biased information processing of gambling cues and reward-related sensitisation mechanisms, by identifying whether they are susceptible to change and generate hypotheses to be tested in further clinical studies.

CBM has been demonstrated to successfully reduce the coding of alcohol-related salient cues in the brain reward system [71] and impact on addiction behavioural outcomes [34–36]. Cognitive profiling of pathological gamblers identified deficits in response inhibition to motivationally salient cues, reward-related switching, and value-based decision-making processes [37]. Therefore, it seems reasonable to hypothesise that interventions targeting value-based and implicitly learnt stimulus-response associations could positively impact the “imbalance” in the value system and likely reduce the risk to relapse and/or escalating in gambling behaviour. Furthermore, CBM interventions are simple, inexpensive, and easy to access anywhere and anytime via the Internet, thus offering a larger outreach and greater availability, convenience, and accessibility, than standard face-to-face interventions. These aspects are important to clinical practice and for healthcare policy makers, since problematic and pathological gamblers are a notoriously difficult population to reach, who hardly ever seek help through standard healthcare facilities and resources, and when they do, the majority of gamblers drop out of treatment. Brief e-health interventions have the potential to be a valuable and cost-effective solution, accommodating the needs and characteristics of this particular population.

An innovative feature of the CBM interventions presented here concerns the introduction of some degree of personalisation in the selection of the stimuli used in the training tasks. The choice of task stimuli for both assessment and training is a key element in CBM interventions. Stimuli should be easily recognisable, sufficiently diverse in content, and representative of the environmental cues and behavioural patterns associated with the addictive behaviour of interest [53]. To this end, a substantial number of stimuli encompassing four broad categories of gambling games, plus an additional category for a local gambling practice (i.e., Belgian bingo), have been created to maximise generalisability of training effects on diverse gambling cues and scenarios [34, 35]. The gambling stimuli were developed according to a validated CBM stimulus development protocol [53] and previous studies on gambling cue reactivity [6]. Within each gambling category, pictures portray several gambling contexts, circumstances, and objects, and typical gambling venues and exemplars of popular gambling websites in Belgium and the Netherlands. However, gambling practices and instances are so numerous and heterogeneous, that using such a variety of stimuli would not properly match the gambling habits of different people. For example, one participant might regularly play poker and dice, but never bet on horse races or play slot machines. Incentive-motivational models of addiction argue that biased motivational cognitive processes such as attentional bias and approach bias are proportional to the learned association between specific gambling cues and the resulting rewarding effects [23]. Therefore, cognitive biases will be only exhibited towards cues consistently associated with rewarding effects, and not towards cues that participants have limited or aversive experiences with. Similar to previous studies evaluating stimulus-specific attentional bias towards alcohol [72–74], in the current study participants choose two gambling activities that are most problematic or could become a problem. Personalising the stimuli used in CBM tasks may thus optimise the effects of the training intervention and also improve the construct validity of the assessment tasks.

To conclude, this is the first study exploring, with a personalized approach, the effects of two online CBM interventions for individuals with different degrees of gambling problems. Results will allow further exploration of the underlying theoretical assumptions of CBM interventions, i.e., dual-process models of addictive behaviours, and their applicability to gambling disorder. In addition, results will provide preliminary data on both the implementation feasibility and effectiveness of a new treatment approach, which, also from a health-economic perspective, might be highly interesting.

## Trial status

Recruitment is open and data collection is currently ongoing (started in February 2015). We expect it to be completed at the end of 2017.

## Abbreviations

AAT: Approach avoidance task
ABM: Attentional bias modification
ANOVA: Analysis of variance
AppBM: Approach bias modification
AUDIT: Alcohol Use Disorder Identification Test
BDI-II: Beck Depression Inventory-II
BIS-11: Barratt Impulsiveness Scale
CBM: Cognitive bias modification
GD: Gambling disorder
G-RCQ: Gambling Readiness to Change questionnaire
MI: Motivational interviewing
RCT: Randomized controlled trial
RSES: Rosenberg Self-Esteem Scale
RT: Reaction time
SOGS: South Oaks Gambling Scale
SPIRIT: Standard protocol items: recommendation for interventional trials
SUD: Substance abuse disorders
VPT: Visual probe task
